### Blood sample collection and laboratory measurements

Blood collection using an intravenous catheter (VACUTAINER, Becton Dickinson, Franklin Lakes, NJ, USA) is scheduled at the day of the enrollment and then during two follow-up visits, after 6 and 12 weeks. Laboratory tests are provided with the use of whole blood, serum, and plasma. Blood is collected in a fasting state, at least 12 h after the last meal, from the ulnar vein, in a volume of approximately 10 mL. Patients are also advised to abstain from alcohol and avoid excessive physical effort within 48 h preceding the blood collection. Serum tubes are allowed to clot for 30 min in a vertical position at room temperature. Serum is separated from venous blood samples by centrifugation for 10 min at 3000 × g at room temperature. Following the centrifugation, routine laboratory measurements are performed in fresh serum (glucose, creatinine, basic lipid profile [total cholesterol, LDL-C, HDL-C, TGs], AST, ALT, GGT, CK), and only HbA1c is measured in whole blood. All remaining serum is aliquoted and stored at —80 °C until assayed for hs-CRP, Apo AI, ApoB, lipoprotein(a), and sd-LDL-C. All measurements (except for HbA1c) are performed on the Horiba ABX Pentra 400 analyzer (Horiba ABX, Montpellier, France). LDL-C is measured directly and non-HDL-C is calculated. Reagents for lipoprotein(a) and sd-LDL-C (direct automated sdLDL-C kit) are supplied by Randox Laboratories (Crumlin, UK). HbA1c is measured on the BIO-RAD D-10™ Hemoglobin Testing System using high-performance liquid chromatography (HPLC).

Laboratory measurements are performed at the Department of Laboratory Medicine, Nicolaus Copernicus University, Collegium Medicum, Bydgoszcz, Poland, holding national and international procedures for quality control assays.

Blood samples for fluorescence measurements are collected at predefined time points. Plasma is separated from venous blood samples by centrifugation for 10 min at 3000 × g at room temperature. Plasma is filtered with the use of micro-dialyzers (Xpress Micro Dialyzer MD100, cut off 12–14 kDa) before fluorescence measurements. It is important to apply the preliminary fractionation to remove the majority of unnecessary particles from plasma just before the final measurement. In order to measure the fluorescence lifetime of samples, the stationary fluorescence spectrometer Hitachi F7000 and time-resolved spectrometer Life Spec II (Edinburgh Instruments Ltd) with the subnanosecond pulsed EPLED diode emitting a light of wavelength λ = 360 nm are used. The spectrometer Life Spec II is equipped with an electronically cooled photomultiplier Hamamatsu R928 connected with a TCC900 PC Card, which incorporates all the electronic modules required for time-correlated single photon counting (TCSPC). Additionally, the concentration of hydroxyproline in all samples is determined. Assessment of plasma fluorescence is provided at the Department of Pharmacology and Therapy, Nicolaus Copernicus University, Collegium Medicum.

### The statistical analysis

Since there is no reference study examining the effectiveness of combined treatment of hypercholesterolemia with rosuvastatin and ezetimibe according to timing of drug administration, we decided to perform an internal pilot study of 20 patients to estimate the final sample size. The means and standard deviations of reduction in LDL-C were 53.25 ± 31.49 mg/dL and 57.71 ± 30.35 mg/dL during morning and evening administration, respectively. The correlation coefficient between total cholesterol reduction during morning and evening drug administration was 0.901. Based on these results and assuming a two-sided alpha value of 0.005, we calculated using the *t* test for dependent variables that enrollment of 157 patients would provide a 98% power to demonstrate a significant difference in total cholesterol level. To compensate for potential withdrawal of consent or loss of study participants due to other reasons, we plan to enroll 200 patients.

The statistical analysis will be carried out using the Statistica 12.0 package (StatSoft, Tulsa, OK, USA). Normal distribution of quantitative variables will be assessed with the Shapiro-Wilk test. Depending on the results of the Shapiro-Wilk test parametric, the Student *t* tests, the one-way analysis of variance (ANOVA) or a non-parametric test (the Mann-Whitney *U* test, Wilcoxon’s signed rank test, or the Kruskal-Wallis ANOVA, multiple comparison test) will be used. The χ^2^ test, the χ^2^ with the Yates correction, or Fisher’s exact test will be used for qualitative variables depending on subgroup size. To assess factors influencing plasma fluorescence parameters, correlation analysis and multiple regression analysis will be conducted. Two-sided differences will be considered significant at *p* < 0.05.

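### The sample size rests on the treatment difference seen in a 20-patient internal pilot; if those patients enter the final unadjusted test, its type I error is modestly above 5%

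*Protocol article*

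**What the plan says.** All of this is in the protocol article, under the heading The statistical analysis.

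- The reason for the pilot: "Since there is no reference study examining the effectiveness of combined treatment of hypercholesterolemia" according to dosing time, and so "we decided to perform an internal pilot study of 20 patients to estimate the final sample size".
- The pilot results are given by dosing time: "reduction in LDL-C were 53.25 ± 31.49 mg/dL and 57.71 ± 30.35 mg/dL during morning and evening administration". A within-patient correlation follows: "The correlation coefficient between total cholesterol reduction during morning and evening drug administration was 0.901".
- The size is derived from them: "Based on these results and assuming a two-sided alpha value of 0.005", a paired t test leads to the statement that "enrollment of 157 patients would provide a 98% power to demonstrate a significant difference in total cholesterol level". To allow for losses, "we plan to enroll 200 patients".
- The final tests are ordinary two-sided tests at p < 0.05.

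The section gives no rule for how the size would have responded to other pilot results, and no adjustment for the pilot look. It does not say whether the 20 pilot patients are in or out of the primary analysis.

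**The concern.** An internal pilot that re-estimates only the variance hardly disturbs the type I error. Here the pilot supplied the treatment difference as well. When a large chance difference in the first patients leads to a small trial, those patients carry more weight in the pooled result. When the chance difference is small, the trial grows and dilutes them. The pooled test, read as if its size had been fixed in advance, then rejects a true null hypothesis more often than its nominal level.

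There is a second consequence. The power claim takes a difference from 20 patients as the truth. If that difference is imprecise, the reader of the protocol should be told so next to the 98%.

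**Working it through.** **Inputs**, all from The statistical analysis: mean reductions 53.25 and 57.71 mg/dL; SDs 31.49 and 30.35; correlation 0.901 (labelled total cholesterol, while the means are LDL-C; used here as printed); pilot n = 20; 157 evaluable; 200 enrolled.

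**1. Reproduce the stated size.**
- Difference: 57.71 - 53.25 = 4.46 mg/dL.
- SD of the difference: sqrt(31.49² + 30.35² - 2 × 0.901 × 31.49 × 30.35) = sqrt(991.62 + 921.12 - 1722.21) = sqrt(190.53) = 13.80.
- Standardised difference: 4.46 / 13.80 = 0.323.
- Paired t test (noncentral t), two-sided alpha 0.05: power 97.98% with 156 patients and 98.05% with 157. So 157 is the smallest number that reaches 98%.
- At the printed alpha of 0.005: power with 157 is 88.3%, and 98% needs 231.

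The stated size therefore follows from the observed 4.46 mg/dL at alpha 0.05. The pilot effect, not just the pilot SD, determined it.

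**2. Precision of the pilot difference.**
- Standard error: 13.80 / sqrt(20) = 3.087.
- t = 4.46 / 3.087 = 1.44 on 19 df, p = 0.16.
- 95% CI: 4.46 ± 2.093 × 3.087 = -2.0 to 10.9 mg/dL.
- If the true difference were half the pilot value (2.23 mg/dL), power at alpha 0.05 would be 52% with 157 and 62% with 200.

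**3. Type I error of the pooled test.** The article states no sizing rule, so one has to be assumed. In each simulated null trial, a 20-patient pilot gives an observed standardised difference d. The total is set to N = ((1.96 + 2.05) / d)², within limits. All patients, pilot included, then enter a paired t test at two-sided 0.05.

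| Assumed limits on N | Type I error |
|---|---|
| 20 up to a cap of 200 | about 6.2% |
| from 20, practically no cap | about 6.6% |
| floor of 100 to 157, various caps | about 5.1 to 5.8% |
| N fixed at 200 in advance | 5.0% |
| Post-pilot patients only, any limits | 5.0% |
| Pilot used for the SD only, target difference fixed | 5.15% |

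Small changes in the formula and simulation error move these figures by about 0.1 to 0.2 points.

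**4. Power without the pilot patients.**
- Planned retention: 157 / 200 = 78.5%.
- New enrolments: 200 - 20 = 180, of whom 180 × 0.785 = about 141 are evaluable.
- Power at 4.46 mg/dL, alpha 0.05: 96.8% with 141, against 98.0% with 157.
- If the 157 evaluable patients include all 20 from the pilot, 137 remain and power is 96.4%.

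**The case against.** The strongest reply is that pooling is nowhere stated. A condensed article may leave the analysis sets to a full protocol or SAP that is not shown, and that document may already exclude the 20 patients. This stands in part: pooling is inferred from the word internal. What does not depend on the inference is that the size was taken from the comparative effect, because the article's own figures show it.

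The second reply is that the inflation is small and hangs on an assumed rule. This also stands. A sponsor who would never have run fewer than 100 to 157 patients faces an error only slightly above 5%.

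Several stronger readings are tempting, and the document does not support them.

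- A reader might note that, given the actual pilot, the pooled test rejects a true null in 6.5% (157 patients) or 6.2% (200) of trials, with the estimate shifted by 4.46 × 20/157 = 0.57 or 4.46 × 20/200 = 0.45 mg/dL. A trial whose size had been fixed in advance shows the same figures once its first 20 patients have given this result. They do not measure harm from the sizing.
- A reader might restrict attention to null trials whose computed size is feasible (no more than 200 to 300) and find 10 to 12%. Much of that is selection: a design fixed at 200 shows 7.3% on the pilots with a computed size of at most 200, although its true error is 5.0%. If larger trials were simply abandoned, the overall error would fall to about 2.7%. The article states no feasibility rule.
- A reader might infer that the design was chosen because the pilot leaned towards evening dosing. The stated reason is the lack of a reference study, the test is two-sided, and the computed size depends on the absolute difference. Direction chose nothing.

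Finally, every power figure is conditional on its assumed effect, and the article does say that its calculation is based on the pilot. That is fair, but it gives no indication of how imprecise the pilot difference is.

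**Conclusion.** The point holds in a limited form. The size of 157 (200 enrolled) was derived from an observed difference whose interval includes zero. The plan states no protection for the final test at p < 0.05. If the pilot patients are pooled, the type I error is modestly above nominal: about 6.2 to 6.6% when the total may fall to 20, and about 5.1 to 5.8% with a floor of 100 to 157.

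This rests on two assumptions: that internal means pooled, and that the sizing followed a 98%-power formula of the kind simulated. The usual reassurance about internal pilots applies to variance-only re-estimation, which is not what was done here.

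The dependence of the 98% on an imprecise pilot difference, and its failure to reproduce at the printed alpha of 0.005, follow from the article's own figures and need neither assumption. This is a worthwhile, inexpensive improvement and not a flaw that undermines the trial.

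**What to change.** 1. State whether the 20 pilot patients are part of the primary analysis.
2. Make the primary morning-evening comparison in the patients enrolled after the pilot (180 enrolled, about 141 evaluable) and report the pooled result as a sensitivity analysis. This returns the type I error to 5%. A combination test with fixed stage weights would keep all the data, but weights chosen now, with the pilot result known, would not be truly pre-specified.
3. Say that the 98% holds only if the true difference is 4.46 mg/dL, and print the pilot interval of -2.0 to 10.9 mg/dL beside it.
4. Reconcile the printed alpha of 0.005 with the calculation and with the final level of 0.05.

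The cost is wording, plus about 1 point of power at the pilot effect with alpha 0.05 (96.8% against 98.0%). If 0.005 were truly the intended level, the loss would be larger, from 88.3% with 157 to about 83.5% with 141. Item 4 should therefore be settled first.

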### Endpoints

The primary outcome of the study is change in LDL cholesterol (LDL-C) at 6 (0 vs 6) and 12 (0 vs 12) weeks, as well as between the 6^th^ and 12th weeks, of study drug treatment (combination of ezetimibe and rosuvastatin), depending on the time of day of study drug administration.

The secondary endpoints include:Change in total cholesterol, high-density lipoprotein cholesterol (HDL-C), triglycerides (TGs), apolipoprotein B (ApoB), apoliprotein AI (Apo AI), non-HDL-cholesterol, small, dense-LDL-cholesterol (sd-LDL-cholesterol), lipoprotein(a) at 6 (0 vs 6) and 12 (0 vs 12) weeks, as well as between the 6th and 12th weeks of study drug treatment (combination of ezetimibe and rosuvastatin), depending on the time of day of study drug administrationAssessment of glucose metabolism parameters: glucose, glycated hemoglobin (HbA1c) at baseline and at 6 (0 vs 6) and 12 (0 vs 12) weeks, as well as between the 6th and 12th weeks of treatment with study drugAssessment of high-sensitivity C-reactive protein (hsCRP) at baseline and at 6 (0 vs 6) and 12 (0 vs 12) weeks, as well as between the 6th and 12th weeks of treatment with study drugAssessment of aspartate aminotransferase (AST), alanine aminotransferase (ALT), gamma-glutamyl transferase (GGT), and creatine kinase (CK) at baseline and at 6 (0 vs 6) and 12 (0 vs 12) weeks, as well as between the 6th and 12th weeks of treatment with study drugAssessment of plasma fluorescence using stationary and time-resolved fluorescence spectroscopy at baseline, at 6 (0 vs 6) and 12 (0 vs 12) weeks, as well as between the 6th and 12th weeks of treatment with study drug

Apart from the analysis in the whole population, the above-mentioned endpoints will be analyzed in subgroups depending on age, sex, and presence of other comorbidities.

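### The sample size rests on LDL-C means and SDs, but the correlation and the 98% power are labelled total cholesterol, so power for the primary outcome LDL-C is not established as written

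*Protocol article*

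**What the plan says.** Under Endpoints, the protocol article states: "The primary outcome of the study is change in LDL cholesterol (LDL-C"). Total cholesterol comes first in the list of secondary endpoints. The section on blood sampling treats the two as separate laboratory measurements and says that LDL-C is measured directly.

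Under The statistical analysis, the sample size is derived from an internal pilot of 20 patients:

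- The means and SDs are for LDL-C: "reduction in LDL-C were 53.25 ± 31.49 mg/dL and 57.71 ± 30.35 mg/dL during morning and evening administration".
- The within-patient correlation is for another variable: "The correlation coefficient between total cholesterol reduction during morning and evening drug administration was 0.901".
- The test is a paired t test, "assuming a two-sided alpha value of 0.005".
- The conclusion is again for the other variable: "enrollment of 157 patients would provide a 98% power to demonstrate a significant difference in total cholesterol level".

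Planned enrolment is then raised to 200 to cover withdrawals and losses. The section closes with an analysis threshold of p < 0.05. It gives no LDL-C correlation, no total-cholesterol means or SDs, and no power statement for LDL-C.

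**The concern.** A paired comparison is powered on the SD of the within-patient difference. That SD depends on both period SDs and on the correlation between periods, and all three must belong to the same variable. Here the SDs are labelled LDL-C, while the correlation and the powered endpoint are labelled total cholesterol.

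The correlation matters a great deal. With SDs near 31 mg/dL and a difference of only 4.46 mg/dL, it is the high correlation that makes a trial of this size feasible. If 0.901 does not describe LDL-C, the power for the primary outcome is simply unknown. If it does, the paragraph names the wrong endpoint twice. In both cases the stated justification of the trial's size does not refer to its primary outcome.

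**Working it through.** **Inputs** (protocol article, The statistical analysis): mean LDL-C reduction 53.25 (SD 31.49) mg/dL in the morning and 57.71 (SD 30.35) mg/dL in the evening; r = 0.901, labelled total cholesterol; n = 157; stated two-sided alpha 0.005; analysis threshold 0.05; planned enrolment 200.

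**Formulas**

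- SD of the difference = √(s₁² + s₂² − 2·r·s₁·s₂)
- Standardised difference d = mean difference / SD of the difference
- Power of the paired t test from the noncentral t distribution, n − 1 degrees of freedom, noncentrality d·√n

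**Step 1: the plan's own figure**

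- Mean difference = 57.71 − 53.25 = 4.46 mg/dL.
- SD of the difference = √(991.62 + 921.12 − 2 × 0.901 × 31.49 × 30.35) = √(1912.74 − 1722.21) = √190.53 = 13.80 mg/dL.
- d = 4.46 / 13.80 = 0.323. Noncentrality at n = 157 is 0.323 × √157 = 4.05.

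| Two-sided alpha | Power at n = 157 | n for 98% power |
|---|---|---|
| 0.005 (stated) | 88.3% | 231 |
| 0.05 (analysis threshold) | 98.05% | 157 |

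At alpha 0.05 the smallest n for 98% power is exactly 157. So 0.901 was combined with the LDL-C means and SDs, and the calculation appears to have been run at 0.05. The stated 0.005 does not give the stated result.

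**Step 2: what this does and does not settle**

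The match shows which numbers went into the formula. It does not show which variable 0.901 was computed from: the same number gives the same 157 under either label.

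**Step 3: range if 0.901 really is the total-cholesterol correlation**

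The LDL-C correlation is then not given. The values of r below are assumptions, applied to the LDL-C means and SDs.

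| Assumed LDL-C r | SD of difference (mg/dL) | Power at n = 157, alpha 0.05 / 0.005 | n for 98% power, alpha 0.05 / 0.005 |
|---|---|---|---|
| 0.80 | 19.59 | 81% / 50% | 313 / 460 |
| 0.85 | 16.97 | 91% / 67% | 236 / 347 |
| 0.901 | 13.80 | 98% / 88% | 157 / 231 |
| 0.95 | 9.84 | >99.9% / 99.7% | 81 / 120 |

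If all 200 planned patients were analysed, power at r = 0.80 would be 89% / 65%, and at r = 0.901 99.5% / 95.7%.

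**The case against.** The strongest reply is that total cholesterol is a slip of the pen for LDL-C. The paragraph opens with LDL-C, gives no total-cholesterol mean or SD, says that the calculation is based on the results just quoted, and reaches 157 exactly from the LDL-C figures with 0.901. The abstract and the Discussion also speak loosely of cholesterol when they describe the trial's question. This reply stands as a possibility. If it is right, the correlation is the correct one, 98% holds for LDL-C at alpha 0.05, and what remains here is two wrong labels and the alpha. But the label occurs twice, once for the correlation and once for the powered endpoint, and nothing in the document confirms the slip.

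A second reply is that 98% is a generous target. This also stands in part. At alpha 0.05, even r = 0.80 leaves 81% power with 157 patients and 89% with 200. At the stated 0.005 the same correlation leaves only 50% and 65%.

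Two stronger readings are tempting, and the document supports neither:

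- A reader might infer that variables were definitely mixed, giving an SD that belongs to neither endpoint. That follows only if the label on 0.901 is correct, which cannot be determined.
- A reader might infer that the trial is underpowered for LDL-C. Nothing suggests that the LDL-C correlation is below 0.901; it could be higher. A 95% interval around 0.901 from 20 patients (about 0.76 to 0.96 by Fisher's z) does not help: it describes sampling error in the correlation as labelled, and does not bound a different LDL-C correlation.

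**Conclusion.** The point holds as an inconsistency in the stated basis of the sample size. The inputs are LDL-C means and SDs, the correlation and the power claim are labelled with a secondary endpoint, and no power is stated for the primary outcome. The 98% therefore cannot be taken as the power for LDL-C on the text as it stands.

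The size depends on two things that the document leaves open: which variable 0.901 belongs to, and which alpha applies.

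- If 0.901 is the LDL-C value, power at 157 is 98% at alpha 0.05 and 88.3% at the stated 0.005.
- If it is the total-cholesterol value, power for LDL-C is unknown. Over assumed correlations of 0.80 to 0.95, it runs from 81% to over 99.9% at alpha 0.05 and from 50% to 99.7% at 0.005.

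All figures take the pilot difference of 4.46 mg/dL and the LDL-C SDs as true and use a paired t test. They do not show that the trial is too small.

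**What to change.** 1. State which variable the 0.901 was computed from.
2. If it is LDL-C, replace total cholesterol by LDL-C in both sentences.
3. If it is total cholesterol, recompute from the 20 pilot patients with the SD of the within-patient difference in LDL-C reduction (or the LDL-C correlation), and report that value.
4. In either case, name LDL-C in the power statement, bring the alpha of the calculation and the alpha of the analysis into agreement, and restate the power that 157 evaluable patients give at that alpha.

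The cost is one calculation on data already held, plus corrected wording. The downside is that the stated power may become less favourable. The article reports that recruitment is still open, so a changed figure could still be acted on.

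### The stated alpha of 0.005 gives 88% power with 157 patients, not the stated 98%, and conflicts with the 0.05 threshold set for the analysis

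*Protocol article*

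**What the plan says.** All the relevant text is in the protocol article, Methods, under The statistical analysis.

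- **Pilot results (20 patients):** LDL-C reductions, mean ± SD, were "53.25 ± 31.49 mg/dL and 57.71 ± 30.35 mg/dL during morning and evening administration, respectively".
- **Correlation:** "The correlation coefficient between total cholesterol reduction during morning and evening drug administration was 0.901".
- **Test:** "we calculated using the *t* test for dependent variables".
- **Alpha for the sample size:** "Based on these results and assuming a two-sided alpha value of 0.005".
- **Result:** "enrollment of 157 patients would provide a 98% power to demonstrate a significant difference in total cholesterol level". Planned enrolment is then raised to 200 to allow for withdrawals and other losses.
- **Alpha for the analysis, at the end of the next paragraph:** "Two-sided differences will be considered significant at *p* < 0.05".

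The article gives no reason for using two levels and mentions no multiplicity adjustment.

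**The concern.** An alpha of 0.005 is unusual for a single paired comparison, and it is a tenth of the level set for the analysis. Two things follow.

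First, alpha, effect size, number of patients and power are tied together. If 157 and 98% came from an alpha of 0.05, they are wrong as printed beside 0.005. The paragraph would then claim a strict error rate and a high power that the design does not deliver together.

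Second, the section names two levels and does not say how they relate. If the sample-size alpha is read as the level for the primary comparison, a primary p-value between 0.005 and 0.05 would be significant by one sentence and not by the other. This should be settled before the results are known, and the article says the trial is still recruiting.

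**Working it through.** **Inputs** (all from The statistical analysis)

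- Mean LDL-C reduction: 53.25 mg/dL (morning) and 57.71 mg/dL (evening)
- SDs: 31.49 and 30.35 mg/dL
- Correlation: r = 0.901. It is labelled as total cholesterol and is applied here to the LDL-C SDs, the only SDs given.
- Paired t test, two-sided; n = 157; stated power 98%; planned enrolment 200

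**Step 1. Standardised effect**

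- Difference: 57.71 − 53.25 = 4.46 mg/dL
- Variance of the within-patient difference: 31.49² + 30.35² − 2 × 0.901 × 31.49 × 30.35 = 991.62 + 921.12 − 1722.21 = 190.53
- SD of the difference: √190.53 = 13.80 mg/dL
- dz = 4.46 / 13.80 = 0.323

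**Step 2. Power formula**

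Power = P(|T| > t₁₋α/₂,ₙ₋₁), where T is noncentral t with n − 1 degrees of freedom and noncentrality dz × √n. For n = 157 the noncentrality is 0.3231 × √157 = 4.05 on 156 degrees of freedom.

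**Step 3. Which alpha reproduces the plan's 157 and 98%?**

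| Two-sided alpha | Critical t (156 df) | Power at n = 157 | Smallest n for 98% power |
|---|---|---|---|
| 0.05 | 1.975 | 98.05% | 157 |
| 0.005 (as stated) | 2.848 | 88.3% | 231 |

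At alpha 0.05, n = 156 gives 97.98%, just short of 98%, so 157 is exactly the minimum. The plan's figure is reproduced at 0.05 and not at 0.005.

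**Step 4. Full enrolment**

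With all 200 patients evaluable, power is 95.7% at alpha 0.005 and 99.5% at alpha 0.05. At 0.005 even enrolment without any loss falls short of 98%.

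**Step 5. Can another reading rescue 98% at 0.005?** (n = 157 throughout)

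| Variant | Power |
|---|---|
| Two-sided 0.005, normal approximation | 89.3% |
| Two-sided 0.005, one SD for both periods, averaged variance, or r from 0.900 to 0.9014 | 87.1% to 89.9% (n for 98%: 221 to 238) |
| One-sided 0.005 | 92.4% |
| Two-sided 0.01 | 92.4% |
| Two-sided 0.025 (not stated anywhere) | 96.2% |

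None reaches 98%. With the printed means and SDs, the correlation would have to be about 0.933 (r = 0.93 gives 97.4%, r = 0.94 gives 99.0%). The document prints 0.901 to three decimals, so rounding cannot close the gap.

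**The case against.** The strongest reply is that 0.005 is a misprint for 0.05. If so, the calculation was sound: 157 evaluable patients give 98%, 200 give 99.5%, the trial is not underpowered, and the analysis threshold already agrees. This is the likely explanation, given the exact match. It makes the repair easy, but it does not make the printed sentence right. The paragraph that justifies the sample size gives an explicit error rate that is inconsistent with its own result, and the article alone does not tell a reader which figure is in error.

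A second reply is that 0.005 is only a planning value and that the single rule for the analysis is 0.05. Planning at a stricter level than the test uses can be a deliberate, conservative choice. This has some force: nowhere does the article say that the primary result will be judged at 0.005, so the conflict between thresholds is the weaker half of the point. The arithmetic half is untouched, because a plan really made at 0.005 would have shown 88%, not 98%. The shortfall of 88.3% against 98% is also conditional: it applies only if 0.005 is the level meant.

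A third reply is that r = 0.901 and the power claim are labelled total cholesterol, while the means and SDs are for LDL-C. That is true, so applying r to LDL-C is an assumption, and the result is sensitive to r, as Step 5 shows. But the text says the calculation rests on the results just listed, no other SDs are printed, and this reading returns 157 exactly at alpha 0.05. The labelling needs its own correction but does not change the conclusion here.

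**Conclusion.** The point holds. With the document's own figures, a two-sided alpha of 0.005, 157 patients and 98% power cannot all be true. At 0.005 the power is 88.3%, about 10 percentage points below the claim, and the chance of missing the assumed difference is 11.7% instead of 2%. At 0.05 the claim is exactly right. The sample-size alpha also differs, without explanation, from the level fixed for the analysis in the same section.

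The conclusion assumes that the pilot estimates are taken at face value, that r = 0.901 applies to the LDL-C reductions, and that the test is the paired t test the article names. If 0.005 is a misprint, the planned size stands and only the stated alpha is wrong. If it was intended, the power is overstated and the analysis threshold is inconsistent with it. A correction is needed in either case, because the stated error rate underlies the sample size and bears on how the primary result will be judged.

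**What to change.** State one two-sided alpha in the sample-size paragraph and in the analysis paragraph.

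- **If 0.05 was meant (the likely case):** replace 0.005 with 0.05 in the sample-size paragraph. The 157 patients, the 98% power, the 200 to be enrolled and the analysis threshold then agree.
- **If 0.005 was meant:** restate the power as 88% at 157 evaluable patients (95.7% if all 200 are evaluable), set the primary-analysis threshold to 0.005, and give the reason for that level. Keeping 98% would require 231 evaluable patients, more than the planned enrolment.

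The first option costs one corrected figure and the second a few lines of text. Neither needs extra patients unless 98% power at 0.005 is insisted on. The correction should be made and dated before the primary comparison is examined.

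### A Shapiro-Wilk test on the trial data chooses the primary test, so the test and the quantity it estimates are not fixed in advance, although the sample size assumes a paired t test of means

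*Protocol article*

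**What the plan says.** All of this is in the protocol article.

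- **Selection rule** (The statistical analysis): "Normal distribution of quantitative variables will be assessed with the Shapiro-Wilk test". The next sentence opens "Depending on the results of the Shapiro-Wilk test parametric" and assigns Student t tests or one-way ANOVA to one branch. The other branch holds the Mann-Whitney U test and "Wilcoxon’s signed rank test, or the Kruskal-Wallis ANOVA, multiple comparison test) will be used".
- **Primary outcome** (Endpoints): "The primary outcome of the study is change in LDL cholesterol (LDL-C) at 6 (0 vs 6) and 12 (0 vs 12) weeks", and also between weeks 6 and 12, by time of day of administration. This is a quantitative variable, and no separate analysis is named for it, so the rule covers it.
- **Sample size** (The statistical analysis): the pilot means and SDs of "reduction in LDL-C were 53.25 ± 31.49 mg/dL and 57.71 ± 30.35 mg/dL during morning and evening administration, respectively" go into a t "test for dependent variables that enrollment of 157 patients would provide a 98% power to demonstrate a significant difference in total cholesterol level". Only the paired t test is used there.

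**The concern.** The sample size fixes one test and one quantity, the mean within-patient difference in mg/dL. The analysis text then lets the observed data replace that test with a rank test, which targets a different centre when the differences are skewed. Nobody can say before the data are seen which test will decide the primary question or what its estimate will mean. The same rule runs over all laboratory endpoints, three contrasts each, and subgroups. One marker could therefore be tested by t at one contrast and by ranks at another.

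The rule also leaves open which variable is tested for normality, and its list mixes paired and independent-group tests. So the primary test is not settled even before Shapiro-Wilk is applied.

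**Working it through.** **1. The plan's own figure.** Inputs from the sample-size paragraph: mean reductions 53.25 and 57.71 mg/dL, SDs 31.49 and 30.35, correlation 0.901 (stated for total cholesterol).

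- Difference = 57.71 − 53.25 = 4.46 mg/dL.
- SD of the paired difference = √(31.49² + 30.35² − 2 × 0.901 × 31.49 × 30.35) = √190.5 = 13.80 mg/dL.
- Standardized difference = 4.46 / 13.80 = 0.323.
- Paired t test, n = 157 (noncentral t): power 98.05% at two-sided alpha 0.05, and 88.3% at the stated two-sided 0.005.

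The 157 patients and 98% thus reproduce with the paired t test at 0.05. The stated 0.005 is a separate discrepancy. Either way the design test is the paired t test.

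**2. Shape of the paired difference in this crossover.** Write P for LDL-C in period 1 minus period 2, τ for the timing effect (morning minus evening), π for the period effect and ε for the remaining variation.

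- Morning first: morning − evening = P = τ + π + ε.
- Evening first: morning − evening = −P = τ − π − ε.

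With equal allocation, no carryover and the same τ in every patient, the pooled difference is symmetric about τ, whatever the shape of ε and whatever π is. Mean, median and Wilcoxon pseudomedian then coincide.

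**3. How often Shapiro-Wilk (p < 0.05) would move the analysis to ranks, n = 157.** The article gives no distribution, so every shape and period effect here is an assumption. Normal differences give about 5%. Other simulated rates:

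| Assumed shape | Shape applied to the pooled difference | Shape applied to P, no period effect | Shape applied to P, 5 mg/dL period effect |
|---|---|---|---|
| t, 8 df | 41–42% | 43% | 32% |
| gamma, skewness 0.45 | 50–52% | 14% | 24% |
| gamma, skewness 0.63 | 81–82% | 22% | 43% |

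The last two columns respect the design. Taking the period effect up to 10 mg/dL keeps these shapes within about 13% to 43%. The two t rows differ only by simulation error, since that shape is already symmetric.

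**4. Cost when τ is constant.** At n = 157 (79/78), SD 13.8, alpha 0.05 and period effects of 0 and 5 mg/dL, including gamma skewness 1, the two-stage rule had type I error of 3.3% to 5.9%, within about 1 point of the t test. Power for 4.46 mg/dL was 96.5% to 98.9%, equal to the t test or above it within simulation error.

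**5. Cost when individual timing effects are skewed.** The pooled difference can then be skewed.

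- With mean difference 0, the two-stage rule rejects in about 6% to 17% of trials, against about 5% for the t test. Much of this is a change of target.
- With SD 13.80 and skewness 0.5 to 1, the Wilcoxon pseudomedian lies 0.6 to 1.1 mg/dL from the mean, that is 0.6/4.46 = 13% to 1.1/4.46 = 25% of the planned difference.
- If the skew opposes the effect, power falls to 95% (skewness 0.5) or 88% (skewness 1), while the t test keeps 98–99%.

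**6. Why the fixed test should adjust for period.** With no period effect, half the between-sequence difference in mean P has standard error 0.5 × 13.80 × √(1/79 + 1/78) = 1.10, the same as 13.80/√157 = 1.10 for the paired test. Adjustment therefore costs essentially nothing. With an assumed 10 mg/dL period effect, the unadjusted paired test uses SD √(13.80² + 10²) = 17.04 and standard error 17.04/√157 = 1.36, although the true one is 1.10. It becomes conservative: about 1–2% type I error and 94–96% power, against about 5% and 97–99% for the period-adjusted comparison.

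**The case against.** The strongest reply is that the rule does little harm here. Under opposite sequences and a constant timing effect the paired differences are symmetric, Wilcoxon targets the same centre, and level and power match the t test. That stands, and it limits the point.

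Three stronger readings should be resisted.

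- A reader might infer that the rule will usually abandon the t test, citing rates of 41% to 82%. The two skewed shapes behind that range require the pooled difference itself to be skewed, which a constant timing effect rules out. The article reports only means, SDs and one correlation, so no rate can be claimed as fact.
- A reader might infer that the listed rank tests cannot adjust for period. They can: Mann-Whitney on the week 6 minus week 12 differences, compared between sequences, does so, and it is on the list. The plain paired t test does not adjust either, so period is not a consequence of the pretest.
- A reader might infer that raw values are tested for normality. The text speaks only of quantitative variables, and the week 6 to 12 change is itself a within-patient difference.

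It can also be said that an article condenses a fuller plan. That would excuse silence, but here the article states a data-dependent rule and applies it without exception.

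**Conclusion.** The point holds as a defect of prespecification and estimand. The article makes the primary test depend on a normality test of the trial data, while its sample size assumes a paired t test of the mean mg/dL difference. The pretest protects against nothing at this size: in every shape tried at 157 pairs without a period effect the t test stayed near its nominal 5%, and with a period effect the period-adjusted t-type comparison does so.

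The switch rate is unknown: about 5% under normality, and roughly 13–43% under mild assumed non-normality with a period effect of 0 to 10 mg/dL. Stronger non-normality would raise it. The cost in error rates is negligible if the timing effect is constant, allocation is equal and there is no carryover. It becomes material only if individual timing effects are skewed, with 6–17% rejection of a zero mean difference. Nothing in the article shows whether they are. It should be corrected, but it does not undermine the trial.

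**What to change.** State one primary analysis that applies whatever Shapiro-Wilk shows: a period-adjusted t-type comparison of mean LDL-C, morning versus evening, either as a mixed model with period and sequence or as a between-sequence t test of the period differences. Report the mean difference in mg/dL with its confidence interval.

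Keep a rank test as a named sensitivity analysis, for example Mann-Whitney on the period differences between sequences. Remove the normality test as the selector of the test; distribution plots can still be described. Analysing skewed secondary markers on the log scale is a reasonable option but not required by this point.

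The cost is wording in the statistical section or analysis plan. No extra patients, visits or measurements are needed, and the primary test then matches the t-type comparison of means behind the sample size.
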